## What is the proposed frequency and duration of follow up?

Patients will attend follow up with their respective surgeons as per the surgeon’s clinical follow-up schedule for the given procedure. From a research perspective, the patient follow-up protocol will be implemented following initiation of the VLED. See Figure 1 for the SPIRIT diagram depicting the research follow-up protocol. Patients will be followed for a period of approximately 8 weeks. Patients will have in-person baseline measures, including weight, height, waist circumference, hand grip strength, and symptom screening at the time of preoperative VLED initiation, the day of their surgery, and at 30-days following the date of their surgery. On the day of their surgery, patient data will also be collected with regards to compliance with the preoperative VLED. At the one-month follow-up, patients will also complete standardized follow-up questionnaires that will focus on adverse events, symptoms, and postoperative recovery, as well as the 36-Item Short Form Survey (SF-36). Electronic medical records will be reviewed at thirty-days postoperatively to assess for postoperative morbidity and mortality. Both the clinical and research follow-up will be consistent regardless of the arm the patient is allocated to.

| **Activity** | **Before Randomization** | **-23** | **After Randomization** | | | |
| --- | --- | --- | --- | --- | --- | --- |
|  | **-60 to -23** |  | **-23 to -2** | **-2 to 0** | **0 to discharge** | **+30** |
| Eligibility assessment | X |  |  |  |  |  |
| Informed consent | X |  |  |  |  |  |
| Randomization |  | X |  |  |  |  |
| Intervention (i.e., VLED) |  |  | X |  |  |  |
| Baseline demographic data | X |  |  |  |  |  |
| Operative data collection |  |  |  | X |  |  |
| Baseline anthropometrics (including hand grip strength) | X |  |  |  |  |  |
| Post-intervention anthropometrics |  |  |  | X |  |  |
| Post-surgical anthropometrics |  |  |  |  |  | X |
| Intervention-associated adverse events |  |  | X | X | X | X |
| Postoperative morbidity |  |  |  |  | X | X |
| Surgeon perceived difficulty |  |  |  | X |  |  |
| QoL assessment (i.e., SF-36) | X |  |  | X |  | X |
| Intervention adherence |  |  | X | X |  |  |
| Follow-up completion |  |  |  |  |  | X |

*Figure 1.* SPIRIT figure for participant timeline

*VLED, very low energy diet; QoL, quality of life*

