## What are the proposed practical arrangements for allocating participants to trial groups?

Patient recruitment will occur at Hamilton Health Sciences, St. Joseph’s Healthcare Hamilton, and Kingston Health Sciences. All surgeons who perform elective non-bariatric surgery at these sites will be made aware of the study via workshops and internal communications. Patients will be identified by the surgeons, their administrative assistants, and/or study investigators at the time of referral, at the time of their initial preoperative consultation, or some time following their initial preoperative consultation. Surgeons and/or other clinicians within a patient’s circle of care will introduce the study to participants at the time of their preoperative visits or sometime thereafter. Patients may also reach out directly to study investigators via the contact information provided on the study poster should they choose. Patients meeting inclusion criteria based on a review of their electronic medical record, which will only be accessed by persons within the circle of care or researchers that have obtained permission from the patient, will have their contact information (i.e., email and phone number) recorded and provided to designated research personnel at the time of their initial surgical consultation in clinic. This email contact information will then be passed into a novel automated clinical trials platform developed by Phelix AI©. This platform will automatically send an electronic version of the written informed consent document to the patient as well as a link to schedule an appointment in the following 1-2 days with the research team to discuss the informed consent document via telephone. If the Phelix AI© platform identifies that the patient does not have an accessible email address, this will trigger a notification to the research team and prompt them to call the patient by telephone. At the time of initial contact between the study personnel and patient, the study will be introduced, eligibility will be confirmed. Patients will be provided with the opportunity to ask questions about the previously circulated ICF, and if they have yet to review the document, they will review the document in its entirety with the research team at the time of the telephone contact. If, at the end of this process, patients are understanding of the material risks and benefits of participation, and wish to be enrolled in the study, they will sign the ICF and subsequently be randomized to one of the two arms in this parallel RCT. Following ascertainment of written informed consent, patients will be randomized via a web-based randomization system (randomization.net) in a 1:1 fashion to receive either standard of care plus preoperative VLED or standard of care alone. Randomization will be according to variable block sizes of four and six and will be stratified according to centre.

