All enrolled patients will adhere to the Optifast® 900 or Medimeal® program for three weeks. The weekly cost of the Optifast® 900 or Medimeal® program is approximately $100.00. The cost of the three-week program will be $300.00 ($100.00/wk x 3 weeks = $300.00) per patient and we will continue enrollment until 88 patients, half of which will be in the intervention arm (44 patients x $300.00/patient = $13,200.00).

Patients will be required to make to non-clinically scheduled in person visits for the purposes of the study. Following consent and enrollment, they will require baseline measures of height and weight, as well as symptoms, prior to commencing the study intervention/placebo. They will also require an in-person one-month postoperative follow-up for the purposes of the study that may not align with their scheduled follow up with their respective surgeon. Parking at St. Joseph’s Healthcare Hamilton or Hamilton Health Sciences is approximately $20.00 per visit. Given that each patient will have two visits (2 days x 88 patients x $20.00/patient/day) we will budget $3,520.00.

Patients will be provided with printed study information booklets, Optifast® 900 handouts, diet diaries, and a copy of their informed consent information. The SF-36 and symptom questionnaires will also be administered via paper forms. As such, $1,000.00 is anticipated for printing and associated office supply costs.

Services

Database preparation and entry of all study data will be organized under the supervision of the one of the study investigators, [name], Estimated cost is $3,500.00.

The randomization service provided by randomization.net costs $2,500.00.

Knowledge Translation

The final version of the manuscript from this project will be published in an Open Access journal in order to increase accessibility and aid in knowledge dissemination. The mean publishing fee for large Open Access journals (e.g., BioMed Central, PLoS) ranges from approximately $2,000.00 to $4,000.^55^

The findings generated from this pilot RCT will be presented at an international (e.g., Digestive Disease Week) and a national (e.g., Canadian Surgery Forum) conference. Registration, travel, and accommodations for each is approximately $2,000.00 ($2,000.00/conference x 2 conferences = $4,000.00.

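### Baseline weight and grip strength come before randomisation in Figure 1, but the text's order implies they come after it, when unblinded patients would usually know their arm

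*Protocol*

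**What the plan says.** All references are to the protocol.

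- **Text of *What is the proposed frequency and duration of follow up?***: "Patients will have in-person baseline measures, including weight, height, waist circumference, hand grip strength, and symptom screening at the time of preoperative VLED initiation".
- **Figure 1, same section**: the row "Baseline anthropometrics (including hand grip strength) | X" is marked in the first column, which is headed as before randomisation and covers days -60 to -23. The row "Randomization | | X" is marked in the next column, day -23. The diet row, "Intervention (i.e., VLED) | | | X", is marked only in the column after that. Baseline SF-36 is also in the first column: "QoL assessment (i.e., SF-36) | X". There is no row for symptom screening.
- ***What are the proposed practical arrangements for allocating participants to trial groups?***: the consent form is discussed by telephone; patients who agree then follow this order: "they will sign the ICF and subsequently be randomized to one of the two arms in this parallel RCT". No in-person research visit is described before that step.
- ***Budget justification***, supplies: "Following consent and enrollment, they will require baseline measures of height and weight, as well as symptoms, prior to commencing the study intervention/placebo". This is one of two extra in-person visits budgeted per patient.
- ***What is the proposed duration of treatment period?***: the diet starts three weeks and one day before surgery.
- **Bias section**: patients cannot be blinded. The section on measuring outcomes has a blinded research assistant take anthropometrics and grip strength.

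**The concern.** The schedule and the text give different orders for the same measurements, and a site cannot follow both. The order matters because patients know their arm once it is disclosed.

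- **Grip strength** depends on effort and is the frailty measure listed with the safety outcomes.
- **Symptoms** are self-reported.
- **Baseline weight** is the adjustment variable for preoperative weight loss. A patient who has learned the arm may change eating before being weighed, and an adjustment variable should not be open to influence by allocation.
- **Follow-up completion**, a primary feasibility outcome, requires the pre-diet visit and complete anthropometrics. If the visit comes after randomisation, a patient who misses it is a follow-up failure. If it comes before, that patient is never randomised and lowers the randomisation percentage instead. The order decides which progression criterion bears the loss.

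**Working it through.** The protocol gives no statistical figure to reproduce here. The check is a comparison of sequences plus day counts.

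**Step 1. Place each event, with surgery as day 0.**

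| Event | Figure 1 | Text |
| --- | --- | --- |
| Consent | -60 to -23 | telephone discussion, then signature; no day given |
| Randomisation | -23 | after signature; no day given |
| Baseline weight, height, waist, grip | -60 to -23, before randomisation | when the diet starts |
| Diet start | column opening at -23, after randomisation | three weeks and one day before surgery: -(21 + 1) = -22 |
| Symptom screening at baseline | no row | when the diet starts |
| Baseline SF-36 | -60 to -23, before randomisation | at baseline; no day given |

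**Step 2. Time between randomisation and the text's baseline on day -22.**

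- Randomised on day -23, as in Figure 1: -22 - (-23) = 1 day.
- Randomised at consent, as the allocation section suggests, with consent at the earliest day in Figure 1: -22 - (-60) = 38 days.
- Range: 1 to 38 days. If the diet instead began on day -23, where its Figure 1 column opens, the range would be 0 to 37 days.

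**Step 3. Does another section settle the order?** The allocation section goes from telephone discussion to signature to randomisation with no visit in between. The budget section puts the visit after consent and enrolment and before the diet. Both fit a baseline after allocation. Neither says in words that baseline follows randomisation; that order is inferred.

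**Step 4. Which items actually conflict?** Weight, height, waist and grip strength are dated in both places, and differently. Symptom screening appears only in the text. The nearest schedule row, "Intervention-associated adverse events | | | X | X | X | X", is marked only after randomisation, so symptoms are missing from the schedule and not contradicted by it. SF-36 is not among the items the text ties to diet start.

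**Step 5. Sensitivity of the follow-up criterion.** Above 90% supports the full trial; 80 to 90% means feasible with modifications. Taking all 88 randomised patients as the denominator (an assumption in line with the sample-size section):

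- 8 incomplete: 80/88 = 90.9%, above the benchmark.
- 9 incomplete: 79/88 = 89.8%, in the modification band.

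One missed pre-diet visit can therefore change the category when the rate is near 90%.

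**The case against.** The strongest case on the other side is that this is a loose sentence in the text and not a flaw in design.

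- **No section states that baseline follows randomisation.** Figure 1 leaves room between consent and randomisation, and the budget's reference to enrolment need not mean randomisation. A visit on about day -23 that measures first and then randomises, with the diet starting next day, would satisfy Figure 1 and come close to the text. This is a possible reading, but not the natural reading of the allocation section, which goes from signature to randomisation without a visit. The ambiguity stands.
- **The consequences are limited.** A blinded assistant measures, weight is objective, and clinical outcomes are described without significance testing. This is right and bounds the point. Assistant blinding does not remove changes in patient effort, self-report or eating.

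A reader might also infer more than the documents support:

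- *That the schedule contradicts the text on symptoms.* It does not; it has no symptom row.
- *That the text moves baseline SF-36 after allocation.* Figure 1 has it before randomisation. The outcome-measurement section plans it in person, so it could move with the visit, but no section says so.
- *That under Figure 1, weight drift before the diet is counted as diet effect.* Drift before randomisation is expected equally in both arms. It adds noise and alters within-arm change but does not bias the comparison between arms.
- *That a bias in points or kilograms can be stated.* The protocol gives no input for it.

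**Conclusion.** The inconsistency is real for baseline anthropometrics and grip strength: before randomisation in Figure 1, at diet start in the text. With the allocation and budget sections, the text's order implies that patients would usually have known their arm for 1 to 38 days at baseline. This rests on three assumptions: the diet starts on day -22, randomisation falls between consent and day -23, and patients are told their arm promptly. It arises only if sites follow the text and not Figure 1.

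The exposed quantities are grip effort, reported symptoms, the baseline weight used for adjustment, and where a missed pre-diet visit is counted. The last reaches a primary feasibility outcome; the others concern descriptive safety and clinical outcomes. It is worth correcting before recruitment, particularly if the full trial takes over this schedule, but it does not undermine the pilot.

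**What to change.** State one order in the allocation section, the follow-up text, Figure 1 and the budget justification:

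1. Consent.
2. At the in-person visit, within one fixed window: anthropometrics, grip strength, symptom screening and SF-36.
3. Randomisation and disclosure of the arm only after these are complete.

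Add a baseline symptom-screening row to Figure 1. State that a patient who misses the baseline visit is not randomised and so counts in the randomisation percentage and not in follow-up completion. While editing, reconcile the diet start day between Figure 1 and the treatment-duration section.

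**Cost.** Mostly wording and sequence. The visit is already budgeted (2 visits x 88 patients x $20 = $3,520 for parking); each patient measured but then not randomised would add about $20 for parking plus staff time. The main downside is that allocation is known later, so product supply and the diabetes-educator referral for patients in the diet arm must fit between disclosure and diet start. The arm must also be disclosed in a way that keeps the measuring assistant blinded, for example by the web system or a later telephone call.

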## What are the proposed primary and secondary outcome measures?

Detailed criteria for event adjudication are reported in the associated documented titled “Trial Outcome Definitions”. An outcome adjudication committee will be formulated who will independently identify and report outcomes. This committee will be blinded to treatment allocation. Given that this is a pilot trial, the primary outcome will be feasibility.

Feasibility Outcomes:

1. Randomization percentage: Defined as the number of patients agreeing to participate in the RCT and being randomized to treatment or control divided by the number of patients approached for participation in the RCT. A randomization percentage of 70% or greater will support the feasibility of a full RCT. A lesser randomization percentage may be feasible with modifications.
2. Recruitment rate: Defined as the number of patients enrolled and randomized into the RCT per month. We will aim for a rate of 16 patients per month (i.e., 4 patients per site per month). A recruitment rate of equal to or greater than this will support the feasibility of a fully powered RCT. A recruitment rate of greater than 10 but less than 16 patients per month will be considered feasible with modifications for the larger RCT. A recruitment rate of less than 10 patients per month will suggest that a larger RCT is not feasible. For the full RCT, we anticipate participation of at least 10 sites. If each site recruited 4 patients per month, this would equate to 48 patients per year. Therefore, after 2.5 years of recruitment, we would reach our pre-specified sample size of approximately 1,200 patients.
3. Intervention compliance: Defined as the number of preoperative VLED doses taken divided by the total number of doses prescribed (84) for each participant randomized to the intervention arm. Compliance will be self-reported via written diet diaries (see “Study Diet Diary” document). A mean compliance of greater than 80% (i.e., completing 80% or more of their Optifast® 900 or Medimeal® doses), will be our benchmark for feasibility in the present study. A mean compliance between 70% and 80% will be considered feasible with modifications for the larger RCT. A mean compliance of less than 70% will suggest that a larger RCT is not feasible.
4. Follow-up completion: Defined as completion of the pre-VLED, preoperative, and thirty-day postoperative visits, along with complete anthropometric measures and study questionnaires. A follow-up completion rate of greater than 90% will support the feasibility of a larger RCT. A follow-up completion rate of 80-90% will be considered feasible with modifications for the adequately powered RCT. A follow-up completion rate of less than 80% will suggest that a larger RCT is not feasible.

Safety Outcomes:

The primary safety outcome will be adverse events deemed secondary to the Optifast® 900 or Medimeal® programs. The adverse events will be recorded as dichotomous outcomes and described as either minor or serious, in a similar fashion to the OPTIWIN Study; the largest medical weight loss RCT evaluating Optifast®.^41^ Standardized definitions for minor and major adverse events are described in “Adverse Events” associated document. We will also measure patient frailty with grip strength at the time of anthropometric measurement.^43^

Clinical Outcomes:

The efficacy outcomes will include:

1. Overall 30-day postoperative morbidity. This will be defined as any deviation from the usual postoperative course within 30-days of the index operation and will be a composite of system-specific complications (see “Trial Outcome Definitions” document)
2. 30-day system-specific complications (see “Trial Outcome Definitions” document)
3. 30-day postoperative mortality
4. Preoperative weight loss. Preoperative weight loss will be assessed by measuring the post-VLED weight on the date of surgery and adjusting for the baseline weight in kilograms, as measured in a standardized fashion by a blinded research assistant.
5. Operative time. Operative time was chosen as an outcome as it is a commonly used objective surrogate for operative difficulty across various types of surgery.^44–46^ It has been used in previous bariatric RCTs as the primary outcome.^47^ Operative time will be measured as the time between first skin incision and closure of the last surgical wound in minutes and will be retrieved from the patient electronic medical record.
6. Intraoperative blood loss. This will be measured in milliliters and will be ascertained from the patient chart.
7. Postoperative length of stay (LOS). This will be measured in days and will be ascertained from the patient chart. Postoperative LOS will be calculated as the number of days following the index surgery (i.e., postoperative day 0) that the patient remains in hospital. Every morning that the patient remains in hospital will count as an added day to postoperative LOS.
8. Quality of life. This will be assessed at baseline, following completion of the VLED, and 30-days postoperatively using the SF-36 (see associated “SF-36” document) administered by a blinded research assistant. The SF-36 has been validated in numerous previous cohorts of patients undergoing both non-bariatric surgery.^48,49^

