# LAY SUMMARY

Obesity has reached epidemic proportions worldwide affecting 700 million persons worldwide, representing 11% of the world’s population. The economic costs of obesity are devastating with an estimated $2.5 trillion and over $100 billion in the United States and Canada, respectively. The obese surgical patient is increasingly pervasive, which may have significant economic and clinical consequences. Obesity in the surgical setting can be extremely challenging and is associated with increased risk of both intraoperative and postoperative complications. Weight loss prior to surgery can significantly reduce these risks and contribute to enhanced postoperative recovery. Yet, preoperative optimization for obese patients has been sporadically applied and studied outside of bariatric surgery. In bariatric surgery, a surgical sub-specialty that manages obese patients almost exclusively, an intensive preoperative optimization program exists. As part of this, patients adhere to very low energy diets (VLEDs) with liquid formulations for two-to-three weeks prior to surgery in an attempt to reduce overall fat volume and improve operative conditions. Despite routine use in bariatric surgery, VLEDs have only been employed in a small number of studies evaluating obese patients undergoing non-bariatric surgery. Evidence for this low-cost initiative is promising but inconclusive. As such, we have designed a pilot randomized controlled trial (RCT) aimed at assessing the feasibility and safety of performing an adequately powered RCT for assessing efficacy of VLEDs with liquid formulation in obese patients undergoing elective non-bariatric surgery. If this pilot RCT demonstrates feasibility and safety, we will be armed with the knowledge required to pursue a larger, adequately powered, multicenter RCT with the intent of optimizing this patient population prior to elective non-bariatric surgery. Ultimately, we hope this research program can inform a preoperative optimization pathway for these patients with the aim of improving outcomes and decreasing associated healthcare burden.

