## What is/are the principal research question(s) to be addressed?

### Feasibility Objectives:

The objective of this pilot RCT is to determine the feasibility of a multicenter, blinded RCT comparing obese patients (i.e., body mass index [BMI] greater than 30kg/m^2^) receiving VLEDs versus control prior to elective non-bariatric surgery in terms of perioperative outcomes.

The specific feasibility objectives of this trial are:

1. Determine the feasibility of recruiting patients in a timely manner across local and outside sites.
2. Determine compliance with preoperative VLEDs in obese patients undergoing elective non-bariatric surgery.
3. Determine the feasibility of completion of follow up.
4. Determine our ability to develop a network of participating sites in a multi-site initiative.
5. Determine the safety of administering preoperative VLEDs to obese patients undergoing elective non-bariatric surgery.

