## Are there any risks to the safety of participants involved in the trial?

Patients enrolled in this RCT will be randomized to receive either standard of care plus Optifast®/Medimeal® or standard of care alone. The standard of care arm would not be incurring incremental risk, though patients randomized to Optifast®/Medimeal® are at risk of mild and severe adverse events. Adverse events are listed in a separate document titled “Adverse Events”. The largest (n = 273) medical weight loss RCT utilizing Optifast® to date reports a mild adverse event rate of 76.8% and serious adverse event rate of 4.5% in patients enrolled in a yearlong program.^41^ The most commonly reported mild adverse events included constipation (18.7%), headache (17.4%) and dizziness (16.8%).^41^ Serious adverse events included symptomatic cholelithiasis, pyelonephritis, and seventh cranial nerve palsy.^41^ These data are most relevant to the long-term use of Optifast® and other similar VLEDs. In our systematic review the median intervention length was four weeks.^19^ Only one included study reported the occurrence of serious adverse events, at a rate of 7.8% over an eight-week intervention period.^37^ The remaining 12 studies in the systematic review, six of which included cancer patients, did not report serious adverse events related to liquid formulation weight loss products. Minor adverse events occurred in 0-50% of patients in the included studies, with only two studies reporting rates of greater than 14%.^37,42^ Both of these studies implemented VLED programs spanning eight weeks. Overall, while there are risks associated with VLED use, these risks are mostly limited to minor adverse events when used in the preoperative setting and we are confident that it will be a safe intervention for patients meeting inclusion criteria. Particularly given that the proposed duration of VLED in the present study is three weeks. There are no interactions with Optifast®/Medimeal® and prescribed medications that may put patients at risk. Overall, the risk associated with the use of Optifast®/Medimeal® in this trial should be minimal given that this product is already approved for this indication in this patient population.

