### Control Group

The control group will consist of standard of care for preoperative management of obese patients undergoing elective non-bariatric surgery without prescription of a specific preoperative weight loss intervention. Currently, there are no standardized interventions aimed at optimizing obese patients prior to undergoing non-bariatric surgery. These patients will routinely receive counselling from their surgeon at the time of their preoperative clinic visit targeted towards preoperative weight loss recommendations. Recommendations are not standardized, nor evidence based. There is no intervention lasting beyond counseling at this visit. Patients will not receive prescriptions for preoperative VLEDs, any other weight loss supplement or medication, or any physical activity intervention aimed at promoting weight loss prior to surgery.

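### The primary safety outcome counts only events attributed to the diet product, so it gives no background rate from controls, which matters most before surgery

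*Protocol*

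**What the plan says.** Under *What are the proposed primary and secondary outcome measures?* the protocol states: "The primary safety outcome will be adverse events deemed secondary to the Optifast® 900 or Medimeal® programs." It adds: "The adverse events will be recorded as dichotomous outcomes and described as either minor or serious." The only adverse-event row in the participant timeline (*What is the proposed frequency and duration of follow up?*) is labelled "Intervention-associated adverse events" and is marked from day -23 to day +30.

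The control arm has no exposure to the product. *Control Group* states: "Patients will not receive prescriptions for preoperative VLEDs, any other weight loss supplement or medication."

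The safety objective is to "Determine the safety of administering preoperative VLEDs to obese patients undergoing elective non-bariatric surgery." The Lay Summary says: "If this pilot RCT demonstrates feasibility and safety, we will be armed with the knowledge required to pursue a larger" trial.

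Elsewhere the protocol plans wider data collection:

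- *How will the outcome measures be measured at follow up?* has questionnaires on the presence of adverse events at baseline, before surgery and at 30 days, plus record review. Neither is limited to one arm or to attributed events.
- The follow-up section says: "Both the clinical and research follow-up will be consistent regardless of the arm the patient is allocated to."
- *Trial Management* has all serious adverse events collected and reviewed by an independent data monitoring committee.

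**The concern.** The outcome depends on a causal judgement about something only one arm takes. A judge who knows the allocation must score controls as zero. A judge who does not know it is guessing.

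The protocol wants outcome adjudicators blinded (*What are the proposed methods for protecting against sources of bias?* and the outcomes section). It also gives adverse-event adjudication to the data monitoring committee, without saying whether that committee is blinded or how it attributes events. Blinded adjudication and attribution to an open-label product fit together poorly. After surgery, diet effects must also be separated by opinion from those of anaesthesia and the operation.

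The symptoms the protocol expects most often (constipation, headache, dizziness) also occur without the diet. Only the control arm can show how often, and the outcome as defined does not use it. What is at stake is how informative the safety description will be when the full trial is designed.

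**Working it through.** **1. The plan's own figure.** The sample size rests on follow-up completion, not safety. The Wilson interval is [p + z²/2n ± z√(p(1-p)/n + z²/4n²)] / (1 + z²/n). With p = 0.90, n = 88 and z = 1.96 it gives 82.0% to 94.7%, which matches the stated 82-95%. The pilot size is not in dispute. Allocation is 1:1, so 88/2 = 44 per arm.

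**2. Which outcome covers which period.**

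| Period | All-cause outcome named? | Attributed outcome? | All-cause data planned in both arms? |
|---|---|---|---|
| Randomisation to surgery | None | Yes | Yes: pre-surgery questionnaire, record review, serious events |
| Surgery to day 30 | Yes: morbidity, system-specific complications, mortality | Yes | Yes |

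While patients are on the diet, the attributed count is the only adverse-event outcome named. Serious events go to the monitoring committee but are not listed as an analysed outcome, and they do not cover minor events.

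**3. What the definition does to a by-arm table.** Assume 6/44 = 13.6% minor events on the diet, all attributed. This is close to the 14% that the protocol says only two reviewed studies exceeded. The control rate is not in the documents, so a range is shown. With Wilson limits (l, u) in each arm, the Newcombe interval runs from d - √[(p₁-l₁)² + (u₂-p₂)²] to d + √[(u₁-p₁)² + (p₂-l₂)²].

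| Control count | Difference (points) | 95% CI |
|---|---|---|
| 0/44, forced by the definition | 13.6 | 2.8 to 26.7 |
| 2/44, all-cause | 9.1 | -3.7 to 22.6 |
| 4/44, all-cause | 4.5 | -9.5 to 18.7 |
| 6/44, all-cause | 0 | -14.9 to 14.9 |

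For the first row, the diet arm's limits are 0.064 and 0.267 and the control upper limit is 0.080. The lower bound is 0.136 - √(0.072² + 0.080²) = 0.028. The protocol does not say it will calculate this difference; the table shows what a reader would take from the two proportions.

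**4. Precision of the all-cause comparison.** At assumed rates of 40% and 20% with 44 per arm, SE = √(0.40×0.60/44 + 0.20×0.80/44) = 0.095. The half-width is 1.96 × 0.095, about 19 points. In the same example an attributed count could logically fall anywhere from 0 to 40% on the diet, depending on the assessor.

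**5. What zero serious events would show.** For 0/44 the Wilson upper limit is z²/(n + z²) = 3.84/47.84 = 8.0%; Clopper-Pearson also gives 8.0%. The protocol cites serious-event rates of 4.5% (year-long programme) and 7.8% (eight weeks). At a true 4.5%, no events would be seen with probability 0.955⁴⁴ = 0.13; at 7.8%, 0.922⁴⁴ = 0.03. These figures reflect sample size, not attribution, and the fix does not change them. They bear only on the claim to demonstrate safety.

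**The case against.** The sponsor has a fair case on several points.

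- A reader might infer that the pilot cannot meet its own safety objective. The documents do not support that. The objective is not worded as a comparison, the analysis is descriptive without significance testing, and an attributed proportion in about 44 treated patients is an answer, though an imprecise one.
- A reader might infer that nothing comparable is collected in controls. That is true of the defined outcome but not of the data. After surgery, morbidity and mortality are already all-cause outcomes. Nothing says by-arm tables of all events will be withheld, and an analysis plan that is not shown may include them.
- A reader might infer that attribution errors decide whether the full trial proceeds. The progression criteria concern randomisation percentage, recruitment, compliance and follow-up, with no safety threshold. *How will the results of this trial be used?* says the safety results inform the design. Only the Lay Summary sentence is conditional.
- The associated documents defining adverse events and outcomes are not shown, so the method of attribution cannot be checked. The cited 4.5% and 7.8% come from longer programmes than this three-week diet.

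All of this stands and limits the weight of the point. It does not remove it: the outcome the protocol calls primary for safety still carries no background rate, and before surgery no other adverse-event outcome is named.

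**Conclusion.** The point holds as a fault of definition, of moderate weight. On the primary safety outcome as written, the control arm is uninformative, and attribution is hard to square with blinded adjudication. The effect is greatest for minor events between randomisation and surgery. In the illustration, the same diet-arm count reads as an excess of anywhere from 13.6 points down to 0 as the control count runs from the forced zero to 6/44.

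This rests on 44 patients per arm and on assumed event counts, because the documents give no control-arm rate. A single-arm attributed rate remains describable, and safety informs progression without formally deciding it.

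**What to change.** Before outcome data are seen:

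- Define the primary safety outcome as any adverse event, minor and serious separately, in both arms and regardless of attribution.
- Report it for two periods, randomisation to surgery and surgery to day 30, with a Wilson interval per arm and a descriptive risk difference with its interval (Newcombe, for example).
- Keep product-attributed events as a secondary list.
- Reword the timeline row to match the all-event collection in the outcome-measurement and trial-management sections.
- Have the Lay Summary say that the pilot describes adverse-event rates, noting that 0/44 would exclude only rates above about 8%.

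The cost is wording, since questionnaires, record review and serious-event collection are already planned for both arms. The sponsor should confirm that the questionnaire, which is not shown, asks about events without reference to the product.

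There are drawbacks. Counts will look higher than attributed counts, and the between-arm difference will be imprecise (about ±19 points at the assumed 40% and 20%). Because patients know their allocation, self-reported symptoms may still differ between arms for that reason alone.
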